#### 1- Introduction and justification

A technical aspect of great importance in liver transplantation (LTx) is the maintenance of the hemodynamic status of the recipient during the anhepatic phase. In the conventional technique, the liver is removed *en bloc* with the retrohepatic portion of the inferior vena cava (IVC), interrupting the venous return of the infradiaphragmatic bed. In order to overcome the consequences of this maneuver, a temporary venovenous bypass (VVB) driven by a centrifugal pump is usually used, allowing diversion of the IVC blood flow to the superior vena cava. More recently, the piggyback method of LTx was described, in which the diseased liver is removed with preservation of the retrohepatic portion of the IVC. Thus, flow through IVC can be maintained, precluding the need for VVB and its inconveniences. This methods avoid the risk of extracorporeal circulation such as air and thrombotic pulmonary embolism, and lymphatic fistulas in the axillary and inguinal regions, where incisions for the placement of catheters are performed. In addition, there a lower cost of the procedure (specific catheters, extracorporeal pump machine, equipment operator, and so on).

In contrast to these advantages, there is a concern regarding a higher incidence of hepatic venous outflow blockade in piggyback LTx recipients, which has been

reported by some authors and denied by others. Notwithstanding this controversy, we are unaware of any prospective randomized trial that it looked to compare the frequency of this complication in the two methods.

## 2- Aim

To compare the frequency of hepatic venous outflow blockade after conventional VVB or piggyback LTx.

## 3- Patients and methods

Forty-two LTx candidates, who will participate of the research protocols ***“Evaluation of inflammatory cytokines in two operative methods of liver transplantation: conventional or piggyback”*** and ***“Evaluation of bacterial translocation in liver transplantation”***, and that agree to also participating of this research, will be prospectively studied. These protocols, which have been already analyzed and approved by the Department of Surgery of FMUSP (Faculdade de Medicina da Universidade de São Paulo) and by CAPPesq (Ethics Committee of the Institution - Comissão de Ética para Análise de Projetos de Pesquisa do Hospital das Clínicas da Faculdade de Medicina da Universidade de São Paulo), admitted randomization of both genders patients, with age between 18 and 60 years, to two groups: LTx performed using the conventional or the piggyback method. Randomization will be conducted immediately before the surgery, by using a table of random numbers.

Exclusion criteria include “familial amyloidotic polyneuropathy” diagnosis, liver retransplantation, active infection, technical impossibility of accomplishment of the surgical method predicted by randomization, necessity of temporary porto-caval anastomosis, and reduced (partial) liver graft. As the patients will be shared with these two studies, the same criteria will be adopted in the current protocol.

In the two groups, the pressure gradient between the hepatic vein and the right atrium will be evaluated. All the necessary procedures for these measurements are also required in the two previously approved protocols or are routinely performed in LTx. According to these protocols, a catheter will be introduced into the graft’s right hepatic vein for blood samples collection. In the current research, this catheter will be used for free hepatic vein pressure measurement. Right atrium pressure was obtained in all LTx by using a Swan-Ganz catheter (routine procedure).

Measurement of hepatic vein and right atrium pressure will be performed once, simultaneously with the last blood sample collection required for the other research protocols, it means, 120 minutes after graft revascularization. “Hepatic venous outflow block” will be considered when a FHVP-CVP gradient higher than 3 mm Hg is registered.

The frequency of “hepatic venous outflow block” will be compared between the two groups by Yates-corrected Pearson’s chi-squared test. A 5% significance level will be considered. The sample size (21 patients in each group) would be sufficient expecting an outflow block frequency of 0% and 25% in conventional and piggyback groups, respectively. These ratios were selected considering that the occurrence of

complications of the venous drainage are very rare in conventional transplantation while an incidence as high as 25% has been reported after piggyback.

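### The aim is outflow blockade after transplantation, but the only outcome is one unrepeated pressure gradient at 120 minutes, so the claim should be narrowed and the reading repeated

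*Protocol*

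**What the plan says.** Section 2 (Aim) reads: "To compare the frequency of hepatic venous outflow blockade after conventional VVB or piggyback LTx". It sets no time window. Section 1 motivates this by saying that "there is a concern regarding a higher incidence of hepatic venous outflow blockade in piggyback LTx recipients", and goes on to treat the blockade as a complication whose frequency no randomised trial known to the authors has compared.

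Section 3 fixes the outcome. "Measurement of hepatic vein and right atrium pressure will be performed once", "simultaneously with the last blood sample collection required for the other research protocols", that is, "120 minutes after graft revascularization". Outflow block "will be considered when a FHVP-CVP gradient higher than 3 mm Hg is registered", with a cited source for the cut-off. The hepatic vein catheter is already in place for the other two studies, and right atrial pressure comes from a routinely used catheter. No earlier or later reading is described, and no clinical or postoperative record of outflow.

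The sample size paragraph of Section 3 plans 21 patients per group, "expecting an outflow block frequency of 0% and 25% in conventional and piggyback groups, respectively". The 0% is justified because "complications of the venous drainage are very rare in conventional transplantation". The 25% carries the same reference as the gradient cut-off.

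**The concern.** There are two separate issues.

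- **Scope.** A conclusion worded like the aim would be wider than the data. If the arms do not differ at 120 minutes, a reader could take this to mean that piggyback transplantation does not raise the frequency of outflow complications. A reading at one early time point cannot show that. The timing is explained only by another study's sampling schedule, with no reason that concerns venous outflow.
- **Measurement.** The endpoint subtracts one pressure from another, each read once on a separate line, and compares the result with a cut-off of only 3 mm Hg. The conventional arm is planned at 0%, so any reading pushed above 3 mm Hg by error would be a false block in the arm where none is expected.

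**Working it through.** **1. Aim, outcome and planning rates side by side**

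- Aim (Section 2): blockade after transplantation, no time limit; called a complication in Section 1.
- Outcome (Section 3): gradient above 3 mm Hg, one reading, 120 minutes after revascularisation.
- Planned 0% (Section 3): argued from the rarity of venous drainage complications.
- Planned 25% (Section 3): cites the source that is also cited for the cut-off.

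The outcome is narrower than the aim in time (nothing after 120 minutes) and in kind (a pressure difference, not a diagnosed complication). The planned 0% belongs to the wider construct. That a clinical complication is rare does not imply that no single reading will exceed 3 mm Hg.

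**2. Reading noise**

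The Protocol gives no figure for measurement error, so there is nothing to reproduce. The inputs are:

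- from the Protocol: cut-off 3 mm Hg, one reading, 21 patients per arm;
- assumed: true conventional gradient normal with SD 0.8 mm Hg and mean m from 0 to 1 mm Hg; independent random error with SD e from 0.5 to 1 mm Hg on each of the two lines, also independent between repeat readings.

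A gradient averaged over k paired readings has SD s = √(0.8² + 2e²/k). The share above the cut-off is P = 1 − Φ((3 − m)/s).

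- e = 0.5: s = √(0.64 + 0.50) = 1.068 for k = 1; √(0.64 + 0.167) = 0.898 for k = 3.
- e = 1: s = √(0.64 + 2) = 1.625 for k = 1; √(0.64 + 0.667) = 1.143 for k = 3.

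| m | e | True share above 3 | Single reading | Mean of three |
|---|---|---|---|---|
| 0 | 0.5 | 0.01% | 0.2% | 0.04% |
| 0 | 1 | 0.01% | 3.2% | 0.4% |
| 0.5 | 0.5 | 0.1% | 1.0% | 0.3% |
| 0.5 | 1 | 0.1% | 6.2% | 1.4% |
| 1 | 0.5 | 0.6% | 3.1% | 1.3% |
| 1 | 1 | 0.6% | 10.9% | 4.0% |

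For example, with m = 1 and e = 1, a single reading gives (3 − 1)/1.625 = 1.231 and a tail of 10.9%.

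In patients, the single-reading range is 21 × 0.00248 = 0.05 to 21 × 0.109 = 2.3 of the conventional arm. For means of three it is 21 × 0.0004 = 0.01 to 21 × 0.040 = 0.8. The calculation covers the conventional arm only and does not give the effect on the comparison between arms.

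**The case against.** The strongest reply is that block is explicitly defined, by a sourced threshold applied alike in both randomised arms, and that the analysis compares exactly that quantity. An objective early endpoint on catheters already in place is a feasible choice, and sharing a time point with another study is not in itself an error. This stands. A reader might infer that the trial cannot support its aim at all. The documents do not support that, because the comparison of gradients at 120 minutes is valid.

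A reader might also infer that blocks relieved before 120 minutes will be counted as no block. This would follow from the literal definition if a correction were made and the gradient then fell to 3 mm Hg or less. But the Protocol mentions no such correction, gives no frequency and states no rule for it.

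It is tempting to show the harm by recoding: 6/21 against 0/21 has a Yates p of 0.027, and losing two cases gives 4/21 against 0/21 with p = 0.115. The number of recoded cases is invented. Moreover, the planned 25% of 21 is 5.25, and 5/21 against 0/21 already has p = 0.057. The example mainly shows how fragile the Yates test is at 21 per arm, which is a different matter.

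On noise, the reply is that every input is assumed and that the top of the range is a worst case. That stands too, and the range must be read as an illustration.

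Finally, counting any problem the surgeon corrected as a primary event would bring a judgement made with knowledge of the technique into an objective endpoint, and would depart from the cited definition. This is a good reason not to do so in the primary analysis.

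What the reply leaves untouched is that the aim is wider than the outcome, and that a single reading is a weaker measurement than an average available on the same catheters.

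**Conclusion.** The point holds in a limited form. The mismatch between aim and outcome rests on the text alone: the trial can report the frequency of a gradient above 3 mm Hg at 120 minutes in each arm, but not the frequency of later or clinically diagnosed blockade. The planned 0% is drawn from the wider construct.

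The noise part is a reason to improve the measurement, not a demonstrated bias. About 0.2% to 11% of single conventional-arm readings would exceed 3 mm Hg, against under 0.1% to 4% of means of three. These figures rest on the assumed mean and SD of the true gradient, the assumed error SD, normality and independent errors, none of which the documents supply. It would go too far to infer that noise will create blocks in the conventional arm: at the low end of the range the expected number is 0.05 of a patient.

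**What to change.** - Restate the aim, endpoint and conclusion as a hepatic vein to right atrium gradient above 3 mm Hg at 120 minutes after revascularisation.
- Use the mean of three consecutive paired readings on the existing catheters, with both lines zeroed to the same level.
- List clinically diagnosed outflow obstruction, taken from routine records, as a descriptive secondary outcome.
- Keep the gradient as the primary endpoint. Record any outflow correction made before the reading, and use it only in a sensitivity analysis that counts such cases as events.
- In the sample size paragraph, say that the 0% comes from a complication rate and is being used as an assumption for the gradient.

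The cost is some rewording, two more readings per patient and one more record field. The downsides are a narrower claim, and that averaging reduces random error but does not remove a shared offset or drift.

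### The Yates-corrected chi-squared test has only about 43% power at 21 per group for 0% vs 25%, so the stated sample size is not sufficient for the test the protocol names

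*Protocol*

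**What the plan says.** The statistical paragraph of section 3 (Patients and methods) fixes the whole comparison. Outflow block frequencies "will be compared between the two groups by Yates-corrected" chi-squared testing in Pearson's form. The level is fixed in its own sentence: "A 5% significance level will be considered". On size the paragraph states: "The sample size (21 patients in each group) would be sufficient". The rates on which that statement rests are given as "expecting an outflow block frequency of 0% and 25% in conventional and piggyback groups, respectively". The 25% is the upper end of what has been published: "an incidence as high as 25% has been reported after piggyback". The conventional rate is set at 0% because venous drainage complications are described as very rare there. The endpoint is binary: block "will be considered when a FHVP-CVP gradient higher than 3 mm Hg is registered".

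The protocol states no power, no sidedness and no sample-size formula. It gives no reason for the continuity correction and names no other test for small expected counts.

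**The concern.** At the pooled planning rate of 12.5% the expected number of blocks is 21 × 0.125 = 2.6 per group, below the customary minimum of 5 for a chi-squared approximation. The Yates correction is known to be conservative there, so the question is how much power it costs and whether 21 per group is still enough.

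The introduction describes a dispute over whether piggyback transplantation raises the frequency of outflow block. If the test has low power, a non-significant result is likely even when the assumed difference is real, and it could be misread as support for the safety of the piggyback method.

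**Working it through.** **Inputs** (all from the statistical paragraph of section 3): 21 per group, rates 0% and 25%, 5% level, Yates-corrected Pearson chi-squared, which is two-sided by construction. Power is not stated; 80% is assumed only to reproduce the sample size.

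**1. The plan's own figure.** The usual uncorrected formula is n = [z_α √(2·p̄·q̄) + z_β √(p₁q₁ + p₂q₂)]² / d², with p̄ = 0.125 and d = 0.25, so the roots are √0.21875 = 0.4677 and √0.1875 = 0.4330.
- One-sided 5%, 80% power: (1.645 × 0.4677 + 0.842 × 0.4330)² / 0.0625 = 20.6, so **21**.
- Two-sided 5%, 70% power: also 21.
- Two-sided 5%, 80% power: 27.
- Two-sided 5%, 80% power, continuity-corrected (the planned test): 34.

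The figure of 21 therefore comes out of an uncorrected formula, not one that matches the named test.

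**2. Rejection boundary.** With 0 blocks in the conventional group and b in the piggyback group, the Yates statistic is 42 × (21b − 21)² / [21 × 21 × b × (42 − b)].
- b = 5: 42 × 84² / (441 × 5 × 37) = 3.63, p = 0.057, not significant.
- b = 6: 42 × 105² / (441 × 6 × 36) = 4.86, p = 0.028, significant.

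The expected piggyback count is 21 × 0.25 = 5.25, so the most typical result falls short.

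**3. Power at 21/21.** With a true conventional rate of 0%, power is P(X ≥ b_min) for X ~ Binomial(21, 0.25). Type I error comes from enumerating all 22 × 22 outcomes, at a common rate of 12.5% and maximised over common rates.

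| Test | Smallest b against 0 | Power, 0% vs 25% | Error at 12.5% | Maximum error |
|---|---|---|---|---|
| Yates | 6 | 43.3% | 0.9% | 2.3% |
| Fisher | 5 | 63.3% | 1.8% | 2.3% |
| Boschloo | 5 | 63.3% | 3.0% | 4.8% |
| Barnard (score) | 4 (p = 0.044) | 80.8% | 4.8% | 4.97% |
| N−1 chi-squared | 4 (p = 0.038) | 80.8% | 4.8% | 5.1% |
| Uncorrected Pearson | 4 (p = 0.036) | 80.8% | 4.8% | 5.6% |

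Yates loses 80.8 − 43.3 = 37.5 points against Barnard and 63.3 − 43.3 = 20.0 points against Fisher.

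**4. Other analysed splits** (conventional/piggyback, 0% vs 25%).

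| Split | Yates | Barnard | Loss (points) |
|---|---|---|---|
| 21/20 | 58.5% | 77.5% | 19 |
| 22/20 | 58.5% | 77.5% | 19 |
| 23/19 | 53.5% | 73.7% | 20 |
| 19/23 | 53.2% | 71.7% | 18.5 |
| 20/22 | 48.3% | 83.8% | 35.5 |
| 18/24 | 39.3% | 75.3% | 36 |
| 20/20 | 38.3% | 77.5% | 39 |

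The N−1 test's worst-case error is 6.0% at 20/21, 5.5% at 18/24 and 5.3% at 20/20.

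**5. A conventional rate above zero** (assumed values, 21/21, piggyback 25%).

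| Conventional rate | Yates | Barnard | Loss (points) |
|---|---|---|---|
| 1% | 39.6% | 73.1% | 34 |
| 2% | 35.9% | 65.8% | 30 |
| 5% | 25.7% | 46.6% | 21 |

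**6. Keeping the Yates test.** By exact calculation, 30 per group gives 79.7% power and 31 per group gives 82.4%.

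**The case against.** The Yates test is familiar, prespecified and safe: it never exceeds 5%, so a positive result would be valid. Discrete tests commonly run below their nominal level, and Fisher's maximum here is also 2.3%. All of that stands. A reader might infer that the protocol misstates its significance level, but the document does not support this. It declares a nominal threshold and p is compared with it. The harm is to power only.

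A reader might also take 37 points as the general cost of the Yates test. That figure belongs to an exact 21/21 split and a comparator such as Barnard. Section 3 randomizes from a random-number table, describes no blocking, and lists exclusions that can arise after allocation, such as the allocated method proving technically impossible. An exact 21/21 analysed split is therefore not assured. At 21/20 and 22/20 the loss is 19 points, and Fisher's test there equals Barnard (77.5%). Nor do unconditional exact tests as a class deliver 81%: Boschloo's gives 63.3% at 21/21.

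Sidedness is not stated. If a one-sided 5% level was meant, Yates power at 21/21 is 63.3%, against 92.6% for the uncorrected test. The low power does not depend on the two-sided reading alone.

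Finally, choosing among valid tests is partly preference. This one is more than preference because the same paragraph calls the sample sufficient, and under the named test it is not.

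**Conclusion.** The point holds. As written, the primary test and the sample-size claim do not fit together: at 21 per group and 0% vs 25% the named test has 43.3% power, and the customary 80% would take 31 per group. Part or all of that shortfall can be recovered on the same 42 patients, with error held at or below 5%, by changing the test.

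The size of the gain is conditional. It is 37.5 points against Barnard at exactly 21/21, about 19 to 39 points over the nearby splits examined, and about 20 points against Fisher at 21/21. The 0.9% error rate applies at a common rate of 12.5%, and the 2.3% ceiling applies at 21/21. The 2.6 expected blocks per group is the pooled expectation; the planned rates themselves give 0 and 5.25.

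A reader might infer that changing the test secures 81% power. It does so only if the conventional rate is exactly 0% and the piggyback rate is the highest one reported. The protocol calls the complication very rare in conventional transplantation, not absent.

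**What to change.** Before any pressure data are examined, replace the Yates-corrected test in section 3 with Barnard's unconditional exact test (score statistic, two-sided 5%), computed for the group sizes actually analysed. Do not offer the N−1 chi-squared as an alternative, because its worst-case error reaches 6.0% at 20/21.

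Restate the sample-size sentence with its conditions, for example: with 21 patients analysed per group, Barnard's test at a two-sided 5% level has about 81% power if the true rates are exactly 0% and 25%; power falls to about 73%, 66% and 47% if the conventional rate is 1%, 2% or 5% (assumed values).

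The cost is two sentences and software that computes the test. The downside is a test that is less familiar to readers. Keeping the Yates test instead would need 31 per group, that is 62 patients rather than 42, for 82.4% power at 0% vs 25%.

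### 21 per group is called sufficient for 0% versus 25%, but the named Yates-corrected test has only about 43% power there

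*Protocol*

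**What the plan says.** The statistical paragraph of Protocol section 3 (Patients and methods) fixes all the design inputs together.

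- Test: the frequency of outflow block "will be compared between the two groups by Yates-corrected Pearson’s chi-squared test".
- Level: "A 5% significance level will be considered".
- Size: "The sample size (21 patients in each group) would be sufficient expecting an outflow block frequency of 0% and 25" per cent. The size agrees with the total given earlier in the section: "Forty-two LTx candidates, who will participate of the research protocols" named there.
- Rates: "expecting an outflow block frequency of 0% and 25% in conventional and piggyback groups, respectively".
- Basis for the rates: drainage complications are described as very rare after the conventional operation, while "an incidence as high as 25% has been reported after piggyback".

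The paragraph gives no power and no sidedness, and shows no calculation behind 21.

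**The concern.** The comparison of outflow block between the two techniques is the only aim in section 2, and this test is the only analysis named for it. A reader will take the adequacy statement to mean that the trial would probably detect a 25% block rate if it were real. Yates' correction is conservative with few events, and at the planned rates only about five are expected in 42 patients. An n that looks adequate without the correction may therefore be far from adequate with it.

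What is at stake is how a negative result is read. Section 1 describes the question as disputed and says the authors know of no randomised comparison. If power at the planning assumption is below one half, a non-significant result is the likelier outcome even when that assumption is true. It could then be mistaken for evidence that piggyback does not raise the rate of block.

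**Working it through.** **Inputs, all from Protocol section 3.** n = 21 per group (N = 42), rates 0% and 25%, Yates-corrected chi-squared, 5% level. Two inputs are mine. I treat the test as two-sided, because the chi-squared statistic is two-sided by construction. I use 80% power as a benchmark, because the protocol states none.

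**Step 1. Where 21 can come from.** The pooled normal formula, with p̄ = 0.125 and difference d = 0.25, is

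n = [z_α √(2 p̄(1 − p̄)) + z_β √(0.25 × 0.75)]² / d²

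The two roots are 0.4677 and 0.4330.

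- Uncorrected, one-sided 5%, 80% power: (1.645 × 0.4677 + 0.842 × 0.4330)² / 0.0625 = 20.6, so 21.
- Uncorrected, two-sided 5%, 80% power: (1.960 × 0.4677 + 0.842 × 0.4330)² / 0.0625 = 26.3, so 27. At 70% power it gives 21.
- Continuity-corrected, two-sided 5%: n_c = (n/4)[1 + √(1 + 4/(n d))]². At 80% power, 26.3 becomes 33.8, so 34. At 50% power the result is 21.

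The figure 21 therefore matches an uncorrected calculation, or the corrected formula at about 50% power. It does not match the corrected test at 80%.

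**Step 2. Rejection region of the named test.** With 0/21 in the conventional group and b/21 in the piggyback group, the Yates statistic reduces to

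χ² = 42 (b − 1)² / [b (42 − b)]

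| b | χ² | p |
|---|---|---|
| 4 | 42 × 9 / (4 × 38) = 2.49 | 0.115 |
| 5 | 42 × 16 / (5 × 37) = 3.63 | 0.057 |
| 6 | 42 × 25 / (6 × 36) = 4.86 | 0.027 |

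Significance needs b ≥ 6, an observed rate of at least 6/21 = 28.6%. The planned 25% is 5.25 patients, so the nearest attainable count is 5, which just misses.

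**Step 3. Exact power.** At a true conventional rate of 0% that group's count is always zero, so power = P(Bin(21, 0.25) ≥ 6) = **43.3%**. The continuity-corrected normal approximation gives 51%.

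**Step 4. Sensitivity, by full enumeration of both groups at 21 each, piggyback rate 25%.**

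| Conventional rate | Yates | Uncorrected |
|---|---|---|
| 0% | 43.3% | 80.8% |
| 1% | 39.6% | 73.1% |
| 2% | 35.9% | 65.8% |
| 5% | 25.7% | 46.8% |

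The uncorrected test rejects from b = 4 when the conventional count is zero: χ² = 42 × 4/38 = 4.42, p = 0.036. Its actual size reaches about 5.6% at a common rate near 30%.

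**Step 5. What the named test would need.** Exact Yates power at 0% versus 25% is 79.7% with 30 per group and 82.4% with 31. Holding 21 per group, power against 0% reaches 79.9% at a piggyback rate of 35%.

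**The case against.** Several points on the other side have force.

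*No power is stated, so none was missed.* This is correct as far as it goes. A reader might infer that the protocol promised 80% power and failed to deliver it. The text does not support that: 80% is my benchmark, and power and sidedness may be given in an analysis plan that is not shown. But 43% is below even one half, and an analysis plan could not make the present sentence true for the named test.

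*21 can be obtained from the named test.* This also stands. A reader might infer that 21 arises only from some other test. It does not. The continuity-corrected formula returns 21 at 50% power. In addition, 21 is the smallest n at which the fractional expected result, 0 versus 5.25 events, is significant under Yates: 42 × 4.25² / (5.25 × 36.75) = 3.93, p = 0.047, against p = 0.056 at n = 20. Both are weak criteria, equivalent to roughly even odds of success. The protocol does not say which route was used.

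*The planned result is not shown to be non-significant.* Taken literally, this is right. Exactly 25% of 21 cannot occur, the next count down misses 5%, and the next count up meets it. The case rests on the power, and the p-value at 5/21 only illustrates it.

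*The test might be meant as one-sided.* Nothing in the protocol says so. Halving the Yates p-value would make 5/21 significant and give 63% power, still short of 80%.

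*The number may be dictated by the parent studies.* Patients are shared with two approved protocols, and the measurements are routine or already required there. The document does not say that this fixed n at 42, but it would limit the added burden. A reader might go on to infer that the ethics committee was misled, and the document does not show that. A fixed sample is still a reason to report its power accurately.

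**Conclusion.** The statement of sufficiency is wrong as written for the test that the same paragraph names. Under the protocol's own rates, and at a two-sided 5% level, the trial is more likely to miss the difference than to find it. The 43% is an exact binomial figure. It depends on the two-sided reading but not on any chosen power target. The 80% benchmark matters only for the statements about 31 per group and a 35% piggyback rate.

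The planning rates are also at the favourable end. The protocol calls conventional events rare without saying they never occur, and it presents 25% as the upper end of what has been reported. Realistic power is therefore more likely below 43% than above it. This should be corrected before analysis, because it concerns the trial's single comparison.

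**What to change.** Amend the sample-size sentence in Protocol section 3 in one of two ways.

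1. **Keep the Yates-corrected test.** Replace the sufficiency claim with the actual figure: two-sided 5%, 21 per group, about 43% power for 0% versus 25%, and about 80% only for 0% versus 35%. Add the power at conventional rates of 1%, 2% and 5% (40%, 36% and 26%).
2. **Change to the uncorrected chi-squared test before any analysis.** State about 81% power at exactly 0% versus 25%, together with the fall to 73%, 66% and 47% at conventional rates of 1%, 2% and 5%, and the maximum size of about 5.6%. Quoting 81% alone would repeat the problem in a milder form. With so few events, keeping a correction is also defensible.

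The first option costs only a wording change, though the stated figure becomes less favourable. The second also needs a documented change of test made before outcome data are seen. Neither asks for more patients.
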